# Comparative Study of Postural Garment Versus Exercises for Patients With Nonspecific Cervical Pain: Protocol for a Randomized Crossover Trial

**DOI:** 10.2196/14807

**Published:** 2020-04-16

**Keywords:** cervical pain, postural garment, cervical exercises, posture, musculoskeletal disorder

## Abstract

**Background:**

There is a high prevalence of work-related musculoskeletal disorders among health care professionals. Posture is an essential point to be addressed for health care professionals with musculoskeletal disorders. Cervical pain can result from several conditions. Treatment should include posture modification and home exercise.

**Objective:**

This study aims to compare a new postural garment (Posture Plus Force; Medi, Bayreuth, Germany) with exercises for women with nonspecific cervical pain. The investigators focus on nurses and allied health professionals due to the importance of posture in work-related musculoskeletal disorders.

**Methods:**

This randomized crossover clinical trial has a 3-month treatment sequence and a 3-month washout period. Participants will include nurses and allied health professionals 21 to 55 years of age with cervical pain. Participants are allocated at random to two intervention groups: a postural garment (Posture Plus Force) to be worn for 2 to 4 hours per day for 90 days (P+ group) and five physiotherapy sessions (20 minutes each) to learn stretching and strengthening exercises with instructions to continue at home on a daily basis for 90 days (Ex group). The participants in each group will crossover interventions after a 3-month washout period.
The primary outcomes are postural control and pain intensity. A static posturography will be performed with a scan (SpinalMouse; Idiag AG, Fehraltorf, Switzerland). The visual analogue scale is a psychometric measuring instrument designed to document cervical pain severity in individual participants. 
The secondary outcomes are cervical pain-related disability, catastrophizing, the global perceived effect of treatment, and the evaluation of garment comfort. Physical activity is assessed with the International Physical Activity Questionnaire. 
Assessment of primary and secondary outcomes is performed at T0 (pre-intervention), T1 (immediately after garment fitting for P+ group), T30, T60, and T90. The same measurements are recorded after the washout period and during the second intervention following the same sequence. All patients are provided with a logbook for compliance recording, over the counter drug use, pain evaluation, and sick leave.
Statistical analysis is conducted following intention-to-treat principles and the treatment effects calculated using linear mixed models.

**Results:**

The study design has been approved by the Ethics Commission of Hospital N Sra de Meritxell, Andorra in March 2017. A total of 32 participants are already enrolled in the study. An extension of the study is planned in a Spanish university hospital to achieve a larger sample. Study results are expected to be published during 2020.

**Conclusions:**

The Postural garment is expected to improve cervical pain by enhancing posture.

**Trial Registration:**

ClinicalTrials.gov NCT03560492; https://clinicaltrials.gov/ct2/show/NCT03560492

**International Registered Report Identifier (IRRID):**

DERR1-10.2196/14807

## Introduction

### Cervical Pain

There is a high prevalence of work-related musculoskeletal disorders among health care professionals. For instance, dental practitioners have reported a high prevalence of pain in the neck and shoulder region with rates in 2009 as high as 83% [1]. In our environment, and more concretely in our hospital, we found that during a 1-year period, 18% of the hospital staff were treated in the rehabilitation department, with more than 50% of cases caused by pain in the neck and back [2].

According to the Occupational Safety and Health Administration, musculoskeletal disorders affect the muscles, nerves, blood vessels, ligaments, and tendons [3]. Workers can be exposed to risk factors at work, such as lifting heavy items, bending, reaching overhead, pushing and pulling heavy loads, working in awkward body postures, and performing the same or similar tasks repetitively. In general, the more extreme the posture, the greater force required to complete the task.

In a recent study on dentists, a kinematic analysis underlined the posture in the area of the cervical and thoracic spine [4]. In addition, Freitag et al [5] demonstrated that sagittal trunk inclinations are an important factor in the evaluation of physical strain in nursing staff. All in all, posture is an essential point to be addressed for musculoskeletal disorders in health care professionals.

Cervical pain can result from several conditions. Disorders that cause axial neck pain include cervical strain, internal disc disruption syndrome, cervical facet-mediated pain, cervical “whiplash” syndrome, and myofascial pain. Treatment for neck pain is distinct from treatment for extremity pain or symptoms. Most patients with mild to moderate axial pain improve in 2 to 3 weeks. Treatment should include posture modification and home exercise [6-8].

### Postural Garment

The Posture Plus System adopts advanced solutions focusing on the abdomen, shoulders, and dorsal areas. The Posture Plus Force (Medi, Bayreuth, Germany) is based on the lessons learned from the development of the spinal orthosis Spinomed (Medi, Bayreuth, Germany) regarding strength and posture [9]. The Posture Plus Force is a T-shirt that includes tensional inelastic bands exercising traction for postural realignment. There are different garments available with this aim in the market. However, the Posture Plus Force is unique due to its design. Enhancement of posture is centered using an anatomical and physiological approach that focuses on abdominal and periscapular muscles.

We have tested the garment in a few patients with dorsal hyperkyphosis. We have noticed that participants reported improvements in dorsal symptoms and cervical well-being. The abdominal inelastic bands enhance core muscle contractions that facilitate a correct upright position and realign the cervical segment as well. Moreover, the dorsal bands are positioned in a functional anatomical direction following interscapular forces and enhancing perivertebral contractions instead of pulling back shoulders as other garments tend to do. Both tensional bands improve spine alignment from the abdominal zone to the cephalic position, including dorsal and cervical areas (see Figure 1). People, who do not usually remain consistent in their exercises, improved their posture and maintained a better posture during and after wearing the postural garment.

Given the high prevalence of cervical pain in health professionals previously mentioned, we hypothesized that the use of this garment can be useful for this pathology.

**Figure 1 figure1:**
[figure not shown]
Posture Plus Force garment.

### Hypothesis

The postural garment will improve cervical pain by enhancing posture.

## Methods

Inclusion and exclusion criteria for our study include the following.

### Inclusion Criteria

Nurses and health allied professionals with cervical pain ≥3 on the visual analogue scale (VAS)Women 21 to 55 years of ageVoluntarily signed informed consentAble to wear the garment and perform exercises, and attend follow-up assessments

### Exclusion Criteria

PregnancyMalignancy or other severe diseaseCervical pain with significant extremity symptoms or neurological dysfunctions (cervical radiculopathy and cervical spondylotic myelopathy)Unable to perform exercisesUnwilling to do follow-up assessmentsPsychiatric disorders

Participants will be allocated at random to receive interventions in two groups based on a randomization plan.

One group will wear the postural garment (P+ group). The postural garment (Posture Plus Force) is provided to participants. It has to be worn for 2 to 4 hours per day for 90 days. See Figure 1.

The exercise group (Ex group) will do 5 physiotherapy sessions (20 minutes each) to learn stretching and strengthening exercises for the cervical and dorsal areas, with instructions to continue at home on a daily basis for 90 days. The precise explanation of exercises is shown in Multimedia Appendix 1. Home exercise maintains range of motion and helps patients become active participants in their care.

After a 3-month washout period to reverse any change that may have occurred with the first intervention, the participants will crossover the intervention for another 3-month period.

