### Statistical Analysis

Statistical analyses will be conducted following intention-to-treat principles, and the treatment effects will be calculated using linear mixed models. Sample size is determined with a 2 point expected difference in the VAS for pain and a sample standard deviation of 2.5.

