### Financial Disclosure

No funding is received by investigators or participants.

Medi (Bayreuth, Germany) provides the logbook and postural garments for all participants.

This study has the approval of the hospital medical director. Costs will be recorded and calculated for both interventions. In our environment, typical protocol treatment for cervical pain includes 2 to 3 consultations with a physical medicine and rehabilitation physician, and 15 to 20 physiotherapy sessions. For this study protocol, assessment visits will be higher than the standard procedure, but physiotherapy sessions will dramatically diminish. Moreover, participants will aim to be an active part of their neck pain care. In conclusion, we expect a decrease in costs compared to usual cervical pain approaches in our department combined with the educational self-management of pain.

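### The crossover assumes that a 3-month washout undoes all first-period change; the article's own account of both interventions means this cannot be assumed, and unequal carryover would bias the garment-exercise contrast

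*Protocol article*

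**What the plan says.** The Abstract describes a two-period crossover: "This randomized crossover clinical trial has a 3-month treatment sequence and a 3-month washout period". The interventions and the purpose of the washout appear under Exclusion Criteria: "After a 3-month washout period to reverse any change that may have occurred with the first intervention". No evidence is given that three months is enough, and no return to baseline is required.

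Three other statements bear on this:

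- Exclusion Criteria: women in the exercise (Ex) arm "will do 5 physiotherapy sessions (20 minutes each) to learn stretching and strengthening exercises for the cervical and dorsal areas". They are then told to practise every day at home until day 90. The article does not say whether exercise may continue in the washout or in the later garment period.
- Financial Disclosure: the expected cost saving comes "combined with the educational self-management of pain".
- Postural Garment: people who tried the garment "maintained a better posture during and after wearing the postural garment".

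Outcome Measures names postural control and VAS pain as primary. A second baseline, T0b, is taken after the washout. Under Statistical Analysis, "the treatment effects will be calculated using linear mixed models", on an intention-to-treat basis.

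**The concern.** A two-period crossover estimates the direct treatment difference only if whatever remains from period 1 is absent, or equal in the two sequences, when period 2 is measured. The article relies on absence. Yet one arm consists of learning something that the patient then manages alone, and the other is credited with a posture effect that outlasts wear.

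The two kinds of residue differ. Women who exercise first enter the garment period already trained in the comparator. Women who wear the garment first carry no trial exercise training into period 2, though they may carry a posture effect. Nothing in the article makes these residues equal. If they are unequal, the main contrast mixes the treatment difference with carryover, for pain and for posture alike.

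**Working it through.** **No figure to reproduce.** The article states no target sample size, alpha or power.

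**Inputs from the article.** Expected difference 2 VAS points and SD 2.5 (Statistical Analysis); 32 enrolled (Results).

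**Assumptions.** Two-sided alpha 0.05; 16 per sequence; points read on a 0–10 scale; 2.5 taken as the SD of the within-person difference (equivalent to a between-person SD of 2.5 with correlation 0.5); carryover differences of 0.5 to 2 points. The article gives no carryover figure.

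**1. Bias in outcome levels.** Let tau be the garment's true advantage in pain reduction, and lambda_Ex and lambda_P+ the benefit from each first treatment still present at T90b. Period effects cancel between sequences and are left out.

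- Garment first: garment minus exercise = tau − lambda_P+
- Exercise first: garment minus exercise = tau + lambda_Ex
- Average: tau + (lambda_Ex − lambda_P+)/2

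The bias is half the carryover difference. Equal carryover gives none.

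**2. False-positive rate when tau = 0.** Standard error = 2.5/√32 = 0.442, with 30 degrees of freedom.

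| lambda_Ex − lambda_P+ | Bias | Bias/SE | Rejection rate |
|---|---|---|---|
| 0 | 0 | 0 | 5% |
| 0.5 | 0.25 | 0.57 | about 9% (8.5%) |
| 1 | 0.5 | 1.13 | about 19% |
| 2 | 1.0 | 2.26 | about 59% |

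Simulation (20,000 runs) agrees: 8.4%, 19.1% and 59.5%. With 1 point of carryover in both arms it gives 5.1%. If only the garment carries over, by 1 point, a true garment advantage of 2.0 is estimated as 1.5, so the bias can go either way.

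**3. Change from the period baseline.** Here the bias is half the between-sequence difference in (residual at T90b − residual at T0b). Take tau = 0 and carryover after exercise only:

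- Residual 2 at T0b and 2 at T90b: levels +1.0; change (2 − 2)/2 = 0
- Residual 2 at T0b and 1 at T90b: levels +0.5; change (1 − 2)/2 = −0.5

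A constant residual cancels. A fading one makes the two analyses err in opposite directions. Exercise continued or resumed in the garment period also breaks the cancellation. So does a floor: a woman who entered at the minimum of 3 and kept a 2-point benefit starts period 2 at 1, and cannot improve by another 2.

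**4. Would a carryover test detect it?** The test compares sequence totals. With total SD 2.5 and correlation 0.5, the SD of a person's total is √(2 × 6.25 × 1.5) = 4.33, and the SE of the difference is 4.33 × √(2/16) = 1.53. Power at the 5% level is about 10% for a 1-point and 24% for a 2-point carryover difference.

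**5. First period alone (free of carryover).** SE = 2.5 × √(2/16) = 0.884; 2/0.884 = 2.26; power about 59%. That this matches the last row of the table is arithmetic coincidence: both ratios are 2.26. If T0 correlates 0.5 with T90, the residual SD is 2.5 × √0.75 = 2.17, the SE is 0.765, the ratio is 2.61 and power is about 71%.

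No SD is given for posture, so no corresponding figure can be worked out for that outcome.

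**The case against.** The evidence for persistence is thin. The posture remark concerns informal use in a few patients with dorsal hyperkyphosis, not the trial population, and gives no duration; after wear need not mean three months after. The same sentence describes people who tend not to keep up their exercises, which counts against lasting exercise in the other arm. Home exercise is prescribed for 90 days only, the self-management phrase sits in a paragraph about costs, and remembering an exercise is not the same as keeping its pain benefit. All of this stands. A reader might infer that first-period effects will not reverse; the article supports only that reversal cannot be taken for granted.

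A reader might also infer that the contrast is biased, perhaps in the garment's favour. That is not shown. The text hints at persistence in both arms, and equal carryover leaves the contrast unbiased. The 59% figure is the extreme of the range: it needs a 2-point carryover difference, for instance with exercise benefit wholly retained and no garment carryover at all, which sits badly with the posture remark. The 32 is enrolment to date, not a target, and an extension is planned.

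Nor should change from T0b be ruled out. Under a constant additive residual it is the unbiased analysis, and the comparison of levels is the one that errs.

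Finally, model terms and the handling of baselines may be set out in a fuller protocol or analysis plan, so their absence from the article is not held against it. What remains is an assumption that the article states outright and that its own descriptions put in doubt. A model specified elsewhere would not by itself make that assumption true.

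**Conclusion.** The point holds as a design weakness, not as a demonstrated bias. Complete reversal within three months is stated without support and is in tension with the article's description of both interventions. Any unequal carryover would shift the two-period contrast in levels by half the carryover difference, in an unknown direction and by an unknown amount.

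For pain, the shifts of 0.25 to 1.0 point compare with a planned difference of 2. They rest on the assumed carryover range, an additive residual, 32 participants and a within-person difference SD of 2.5. Baseline correction removes the bias only if the residual stays constant, and a carryover test at this size has too little power to settle the matter. The point affects both primary outcomes and should be resolved before the data are analysed.

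**What to change.** 1. Pre-specify the randomised first-period comparison (T90 adjusted for T0) as the carryover-free estimate. Always report it beside the crossover estimate, and do not use a preliminary carryover test to choose between them.
2. Fix in advance how T0b enters the model, and show the crossover result with and without period-baseline correction.
3. Report T0b minus T0 by sequence for pain and posture, so that readers can see how far each sequence returned to baseline.
4. Use the logbook, which already covers compliance, to record home exercise and garment wear in both treatment periods and through the washout.
5. Replace the statement that the washout reverses any change with an explicit assumption and the grounds for it.

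The cost is mainly wording and some extra logbook entries; T0, T90 and T0b are already scheduled. The drawback is precision. With 16 per sequence, the first-period comparison has about 59% power for 2 points, or about 71% if T0 correlates 0.5 with T90. Unadjusted 80% power needs about 25 per arm, 50 in all (26 per arm by the t distribution), which the planned extension might supply.

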### Collected Variables

The following factors will be assessed for all participants: age, weight, height, BMI, work experience, part-time employment, education, managerial position, pharmacological treatment, global perceived effect of treatment, treatment compliance, and garment comfort.

The level of physical activity is evaluated with the International Physical Activity Questionnaire (IPAQ).

Education will be divided into registered nurse, nonregistered nurse, and allied health professional. Managerial positions will include ward managers and group managers. Pharmacological treatment and sick leave will be recorded when necessary. Other variables will include main and secondary outcome measures.

### Outcome Measures

The primary outcomes will be postural control and pain intensity.

Posture can be evaluated with pictures on the sagittal and frontal plane. Objective measurements of static posturography will be performed with a scan (SpinalMouse; Idiag AG, Fehraltorf, Switzerland). SpinalMouse is a device that, when combined with a PC program, assesses the curvatures of the spine without applying radiation. The device is guided manually on the skin along the spinous process apophysis from C7 to S3. The measuring head follows the contour in the sagittal plane and records clinically relevant data. A software program using a highly sophisticated algorithm uses this information to calculate the clinical parameters. The data obtained have been proven reliable and accurate [10,11] in different population groups [12-14]. The standardization and validated protocol do not include the cervical region, but dorsal kyphosis and lumbar lordosis angles influence the cervical position.

To blind the assessment of posture, the investigator that performs the SpinalMouse scan will not be aware of the participants’ current intervention at each follow-up.

All other outcomes will be recorded by the other investigators.

Pain will be measured by the VAS. The VAS is a psychometric measuring instrument designed to document cervical pain severity in individual participants. It achieves a rapid (statistically measurable and reproducible) classification of symptom severity. A 100 mm horizontal line with verbal descriptors will be used to grade the amount of pain that a patient feels from no pain (left 0 mm) to an extreme amount of pain (right 100 mm).

Secondary outcomes will include cervical pain-related disability, catastrophizing, the global perceived effect of treatment, and the evaluation of garment comfort for the P+ group. Days out of work will be recorded in cases of sick leave.

Cervical pain-related disability will be assessed with the validated Spanish version of the Neck Disability Index (Multimedia Appendix 2). The scale includes 10 questions on different aspects of disability due to cervical pain [15].

Psychosocial factors are significant in predicting the duration and severity of symptoms. A significant relation between catastrophizing and pain-related outcomes has been observed in numerous pain samples [16]. Sullivan et al [17] defined catastrophizing as “an exaggerated negative mental set brought to bear during actual or anticipated painful experience”. Individuals who score high on measures of pain catastrophizing report more intense pain. To assess this dimension related to pain, we will use the Pain Catastrophizing Scale (PCS) (Multimedia Appendix 3). The PCS is currently one of the most widely used measures of catastrophic thinking related to pain. It is a 13-item instrument that yields a total score and three subscale scores assessing rumination, magnification, and helplessness.

Assessment of the global perceived effect of treatment will be performed with a VAS (Multimedia Appendix 4). Garment comfort will be evaluated with a 5-point Likert scale question, an open question, and free comments (Multimedia Appendix 5).

Physical activity will be assessed with a self-reported physical activity questionnaire, the Spanish version of the IPAQ short form [18,19].

The assessment of primary and secondary outcomes will be performed at T1, T30, T60, and T90. The same measurements will be recorded after the washout period during the crossover period treatment (T0b, T30b, T60b, T90b). As previously mentioned, the same investigators will follow up with participants except for the SpinalMouse measurement, which will be performed by a blind collaborator.

All patients will be provided with a logbook for compliance recording, over the counter drug use, pain evaluation, and sick leave.

### Statistical Analysis

Statistical analyses will be conducted following intention-to-treat principles, and the treatment effects will be calculated using linear mixed models. Sample size is determined with a 2 point expected difference in the VAS for pain and a sample standard deviation of 2.5.

## Results

The study design has been approved by the Ethics Commission of Hospital N Sra de Meritxell, Andorra in March 2017. A total of 32 participants are already enrolled in the study. An extension of the study is planned in a Spanish university hospital to obtain a larger sample. Study results are expected to be published during 2020.

